PATH Program for Appropriate Technologies in Health

WEHI Walter and Eliza Hall Institute

WHO World Health Organization

WIRB Western Institutional Review Board

**Protocol Summary**

**Protocol Title:** A Phase 1 randomised, double blinded within dose, controlled, dose-escalation, safety and immunogenicity study of a blood-stage vaccine (MSP2-C1/ISA720) against *Plasmodium falciparum* MSP2 in healthy volunteers (QP07C08)

**Version Number and Date:** Version 4.0, 29 July 2008

**Volunteers:** Healthy malaria-naive male and non-pregnant female volunteers 18 to 45 years of age

**Number of Volunteers:** 30

**Trial Design:** Phase 1, Randomised Double blind Within Dose, Controlled, Dose Escalation Study in healthy volunteers

**Immunisation Schedule:**

| **Group** | **Number of Volunteers** | **Immunisation Schedule** | | |
| --- | --- | --- | --- | --- |
| **Day 0** | **12 Weeks** | **24 Weeks** |
| 1 | 15 | A (12) + D (3) | A (12) + D (3) | A (12) + D (3) |
| 2 | 15 | B (12) + D (3) | B (12) + D (3) | B (12) + D (3) |
| Total | 30 | A: 10 μg MSP2-C1/ ISA720  B: 40 μg MSP2-C1/ ISA720  D: ISA720 Control | | |

**Product Description:** The vaccine preparations to be studied contain an equal mixture of MSP2 from two different lines of *Plasmodium falciparum* (3D7 and FC27), both produced separately as recombinant proteins expressed by *E. coli*. Bulk MSP2 antigens were purified from lysates of transformed bacteria grown in a 50 L fermenter. The MSP2 protein was purified from this mixture by a combination of metal-chelate, anion-exchange and reverse-phase chromatography. Purified MSP2-3D7 and MSP2 FC27 were subsequently mixed and emulsified with Montanide® ISA720 (SEPPIC, France) as a final injectable formulation at 20 μg/ml or 80 μg/ml. ISA720 Control vaccine consists of the buffer formulated in Montanide® ISA720 (SEPPIC) (30/70 w/w)

**Time Period:** A total of 56 weeks including screening vaccinations, study procedures, and follow-up of all volunteers. Each volunteer will be followed for a total of 48 weeks (maximum of 52 weeks including screening).

# Objectives

## 1.1 Primary Objective

To assess the safety and tolerability of 3 immunisations at 2 dose levels of the MSP2-C1/ISA720 vaccine in healthy adult malaria-naïve volunteers.

## 1.2 Secondary Objectives

### 1.2.1. Characterise the humoral and cellular immune responses to the MSP2-C1/ISA720 vaccine

### Determine the vaccine dose level that induces the highest serum IgG concentration to MSP2 by ELISA

Table 1: MSP2-C1/ISA720 Vaccine Dose Escalation Schedule

| Time  (Week) | Cohort 1: (n = 15) | Cohort 2: (n = 15) |
| --- | --- | --- |
| 10 μg MSP2-C1/ISA720 | 40 μg MSP2-C1/ISA720 |
| 0 | Vaccination 1 (n=15) |  |
| 4 |  | Vaccination 1 (n=5) |
| 8 |  | Vaccination 1 (n=10) |
| 11 | SMC | SMC |
| 12 | Vaccination 2 (n=15) |  |
| 13 |  |  |
| 16 |  | Vaccination 2 (n=5) |
| 17 |  |  |
| 20 |  | Vaccination 2 (n=10) |
| 24 | Vaccination 3 (n=15) | SMC |
| 25 |  |  |
| 28 |  | Vaccination 3 (n=5) |
| 29 |  |  |
| 32 |  | Vaccination 3 (n=10) |
| 36 |  | SMC |
| 37 |  |  |
| 41 |  |  |
| 48 | Last Visit |  |
| 52 |  | Last visit (n=5) |
| 56 |  | Last visit (n=10) |

**** Table 1- Timing of vaccinations shown as a minimum. First Vaccinations may be delayed.**

# 2.0 Introduction

## 2.1 Background

The World Health Organisation reported in 2005 that malaria kills more than 1 million people annually and that approximately 3.2 million people living in 107 countries or territories are at risk of infection [1]. Most of the malaria mortality occurs in sub‑Saharan Africa and in children under 5 years of age. Of the four species of malaria parasite that infect humans, *Plasmodium falciparum* is responsible for the majority of these deaths. Mounting drug resistance of the malaria parasite, as well as widespread resistance of mosquitoes to insecticides, make these control strategies increasingly unrealistic. A vaccine that would reduce both mortality and morbidity secondary to *P. falciparum* infection would be a valuable resource in the fight against this disease.

*P. falciparum* has a complex life cycle. Sporozoites, the infectious stage of the parasite, are transmitted to humans through the saliva of infected female mosquitoes while taking a blood meal. Sporozoites travel through the bloodstream to the liver, where they invade hepatocytes and then multiply asexually into merozoites. Six to 10 days after invasion, the hepatocytes rupture, releasing thousands of merozoites into the bloodstream. These merozoites invade erythrocytes, multiply and after 2 days, release progeny merozoites, which subsequently invade new erythrocytes to continue the asexual blood-stage cycle. Clinical symptoms in humans are due to this asexual blood-stage of the parasite’s life cycle. A small percentage of merozoites do not multiply after invading erythrocytes, but instead differentiate into gametocytes. These gametocytes are ingested by a female mosquito during a subsequent blood meal and undergo sexual reproduction in the mosquito midgut, producing a zygote. The zygote matures and releases sporozoites that migrate to the mosquito’s salivary glands, thus completing the life cycle.

The complex life-cycle of the malaria parasite offers several points that could be targeted by vaccine-induced immune responses but the merozoite, which invades the host’s erythrocytes, is considered a particularly important target. MSP2 (Merozoite Surface Protein 2), the antigen in the vaccine to be tested in this study, is one of several proteins on the merozoite surface that are being assessed as components of a vaccine against malaria. MSP2 is a ~28kDa protein which is anchored in the membrane of the merozoite by a C-terminal glycosylphosphatidyl-inositol moiety (2, 3). MSP2 has been detected in all isolates of *P. falciparum* examined and appears essential for parasite viability as attempts to "knock-out" the gene have not been successful (4). The function of MSP2 is unknown but it appears to be specific for *P. falciparum* as orthologues of MSP2 have not been detected in *P. vivax*, or rodent and simian parasites, with the exception of *P. reichenowi* a malaria parasite infecting chimpanzees (5).

MSP2 is highly polymorphic with a central variable region flanked by conserved N- and C-terminal regions. The extremely large number of MSP2 alleles fall into two allelic families, 3D7 and FC27, characterized by different centrally-located sequence repeats and family-specific non-repetitive sequences flanking the repeats (6, 7) and the current vaccine contains a representative of these two families of MSP2 alleles.

Being an abundant protein on the merozoite surface MSP2 is a potential target of antibodies induced by infection or vaccination. The majority of individuals living in regions where there is intense transmission of *P. falciparum* develop high titres of anti-MSP2 antibodies in response to repeated infections by five years of age. Much of the natural anti-MSP2 antibody response is directed against epitopes in the central variable region of the molecule (8-10). Several sero-epidemiological studies have shown an association between antibody responses to MSP2 and resistance to infection or disease (e.g. 11-13). The importance of MSP2 as a probable target of naturally acquired protective immunity is also supported by the patterns of various MSP2 genotypes seen among infected individuals (14). Although some anti-MSP2 monoclonal and polyclonal antibodies have been reported to inhibit merozoite invasion *in vitro* (15-17)we have not been able to demonstrate inhibition of invasion with antibodies raised in rabbits to recombinant forms of MSP2 including the 3D7 and FC27 forms of MSP2 to be tested in this vaccine. This may be because only those anti-MSP2 antibodies with a particular fine specificity are effective at blocking merozoite invasion or because other effector mechanisms, such as antibody dependent cellular inhibition are operating (18)

## 2.2 Vaccine Description

### 2.2.1 MSP2 Antigens

Both EcMSP2-3D7 and EcMSP2-FC27 are highly purified ~24 kDa proteins that correspond to the mature polypeptides of *P. falciparum* (3D7) MSP2 and *P. falciparum* (FC27) MSP2, respectively. Each protein has added a 6-histidine C-terminal tag to allow purification by metal-chelate chromatography. EcMSP2-3D7 has a molecular mass of 24,189 Da, whereas EcMSP2-FC27 has a molecular mass of 23,843 Da. The full details of the sequences of the two antigens are described in the Investigational Brochure.

The two forms of MSP2 were separately expressed in *E. coli* from synthetic genes cloned into the *E. coli* expression plasmid pET22b. The two recombinant proteins were purified from *E. coli* lysates by a combination of chelating, anion-exchange and reverse-phase chromatography. The purification processes were designed to separate monomeric MSP2 from non-product related components (e.g. *E. coli* proteins, DNA and endotoxin), as well as MSP2 aggregates or fragments.

Both recombinant forms of MSP2 have a propensity to form fibrils, which have some but not all of the characteristics of amyloid fibrils. A small amount of the formulated antigen may be in this fibrillar form but independent experts do not consider that this poses significant safety concerns and it is unlikely to invalidate the assessment of immunogenicity.

### 2.2.2 Adjuvant

Montanide® ISA720 (ISA720) is an experimental adjuvant used for generating water-in-oil emulsions. ISA720 contains the metabolizable oil squalene and a surfactant from the mannide monooleate family. Homogenization of the antigens in aqueous buffer with Montanide® ISA720 was used to generate an emulsion with a droplet size of approximately 1 micron, which the manufacturer, SEPPIC Inc., recommends as optimal for stability and immunogenicity. Glycine (final concentration 5 mM) was added to the aqueous phase prior to homogenization because this has been shown to prevent antigen modifications that can occur in Montanide® ISA720 emulsions (19). Antigens in ISA720 emulsions have been shown to induce high antibody titers in several animal species. The formation of a depot at the injection site is considered important for adjuvant action. In addition, the stimulation of antigen presenting cells and other mechanisms may also play a role in adjuvant activity of ISA720 formulations. Vaccine formulations using ISA720 as an adjuvant have been given safely to humans, and have been used in human trials with a variety of experimental malaria vaccines, including a combination vaccine consisting of MSP1, MSP2 and RESA (20-32), as well as with a candidate HIV vaccine (33).

### 2.2.3 Vaccine Formulation

For the formulation of the vaccine, EcMSP2-3D7 and EcMSP2-FC27 were mixed in equal amounts and emulsified with the Montanide ISA720 to generate the final drug product. As the trial is a dose-escalating study two different formulations were prepared, with total protein concentrations (EcMSP2-3D7 plus EcMSP2-FC27) of 10 g, and 40 g per 0.5 ml dose. For the ISA720 Control, the aqueous buffer without antigen was emulsified with ISA720. The formulated vaccines were dispensed without preservative into single dose vials and stored at 2-8oC.

## 2.3 Rationale

### 2.3.1 Preclinical Experience with MSP2-C1

The EcMSP2-3D7 and EcMSP2-FC27 antigens have been tested individually or in combination using various adjuvants in rabbits, mice and guinea pigs. The combination of the two antigens (MSP2-C1) formulated in ISA720 has been tested in rabbits and mice. A total of six individual preclinical animal studies have been conducted to assess the safety, immunogenicity or toxicity of the MSP2-C1 or the individual antigens formulated in ISA720. These studies have demonstrated the safety of MSP2-C1 when adjuvanted with Montanide® ISA720. Immunogenicity data from rabbits and mice have demonstrated that each animal species developed anti-MSP2 antibody responses without the occurrence of clinically significant safety issues. Repeated intramuscular administration of the maximum human dose to rabbits in a toxicology study did not result in any specific signs of systemic or local toxicity.

### 2.3.2 Clinical Experience with Other MSP2 Vaccines

The MSP2-C1 combination vaccine formulation that will be used in this study has not yet been tested in human trials. However, both Phase 1 and Phase 2 studies have been carried out previously with vaccines containing a recombinant form of 3D7 MSP2 known as Ag1624. Ag1624, like the forms of MSP2 in the current vaccine was expressed in *E. coli* and was purified by a series of chromatography steps. Ag1642 differs from EcMSP2-3D7 and ECMSP2-FC27 in that the hexa his tag is located at the N-terminus rather than the C-terminus. Also, a small number of additional residues encoded by the plasmid cloning vector are present at both the N- and C-terminus in Ag1624.

Recombinant MSP2 was injected into humans for the first time when Ag1624 in combination with recombinant CS protein (Combination A), formulated with alum was tested in healthy Swiss volunteers (20). Thirty three participants received two low (20 g) or two high (100 g) vaccinations intramuscularly, while six volunteers received placebo (alum alone). Twenty-six participants reported 51 immunisation-related adverse events, mainly pain at the injection site. There were no serious adverse events and the vaccine was considered safe for further evaluation. However, the development of this vaccine ceased because immune responses were poor and no protection was observed among five subjects who were experimentally challenged with *P. falciparum*.

Subsequently, a series of Phase 1 and 2 trials were carried out with a combination of three recombinant antigens (Combination B) that included 3D7 MSP2. In addition to Ag1624 Combination B contained 190L (a small fragment of MSP1) and Ag1505 (a large fragment of RESA). All three components of Combination B were formulated as a water-in-oil emulsion with Montanide® ISA720, the adjuvant to be used in this study. Two Phase I vaccine trials were conducted at the Royal Brisbane Hospital to test the immunogenicity and safety of the Combination B vaccine in healthy Australian volunteers (21).

The first trial tested the safety and immunogenicity of the mixture of three antigens given at a single site or given separately at three sites. For the first vaccination, volunteers received 3 x 100 g of antigen or 3 x 50 g; all received 3 x 20 g in the second vaccination. In the second trial, which compared the safety and immunogenicity of different doses of a mixture of the three antigens, the subjects received 3 x 50 g, 3 x 13 g or 3 x 4 g for the first vaccination and 3 x 20 g, 3 x 13 g or 3 x 4 g for the second vaccination, respectively. No serious adverse events were reported in either trial but local reactions, particularly pain and tenderness, occurred in the majority of subjects, These reactions lasted for up to a few days and were also seen in subjects receiving the adjuvant alone. One subject had a local reaction that was severe for three days before resolving gradually over three weeks.

In both trials some subjects had delayed local reactions with pain, tenderness and/or swelling developing 10 days or later after vaccination. These reactions were clearly related to antigen dose with the majority occurring in subjects receiving the mixture of 3 x 100 g antigen in a single site and none occurring in subjects receiving the lowest antigen dose or the adjuvant alone. The delayed reactions were mild to moderate in all but two subjects. One developed severe pain and swelling in the injected thigh 10 days after the vaccination, which resolved over a week. This subject was given 20 g of each antigen as a second vaccination and six weeks later developed a hard painful mass at the second injection site. The pain and the mass resolved over a few weeks with no biochemical evidence of muscle damage. The other with a severe delayed reaction developed pain and swelling in the thigh and around the knee two weeks after vaccination. There was marked discomfort on use. Symptoms resolved over two weeks with no biochemical evidence of muscle damage.

In a subsequent placebo controlled, double blind trial with Combination B at the Royal Brisbane Hospital, the vaccine was tested for its ability to inhibit parasite growth rates in human volunteers (22). Volunteers each received two vaccinations, 6 weeks apart with 13 µg of each component of Combination B or adjuvant alone and four weeks later were challenged intravenously with approximately 100 *P. falciparum*-infected red cells. Parasitaemias were monitored with a quantitative PCR assay (23) from day four until day eight when the volunteers were treated to eliminate the infection. No significant decrease in parasite growth rates was seen, nor was there any significant correlation between growth rates and any of the measured immunological responses. These results suggested that formulations with significantly greater immunogenicity would be required for these antigens to provide a protective effect. Of the 12 volunteers in this challenge trial the majority had localized pain and tenderness after vaccination which in one was sufficient to preclude a second injection. No other adverse events judged to be related to the vaccine were observed. A second volunteer had a moderate local reaction after the second injection which resolved over seven days.

Although the Combination B vaccine failed to reduce parasite growth rates in Australian volunteers it was considered possible that the vaccine may be more effective in individuals living in a malaria-endemic setting. For this reason Combination B, again with Montanide® ISA720 as the adjuvant, was assessed in two trials in Papua New Guinea. The first of these trials (24) was a Phase 1b study in which 10 adult males from the Wosera region of the East Sepik province were injected twice, four weeks apart, with the vaccine; two individuals were injected with the adjuvant alone. While good cellular immune responses were seen to RESA and MSP1 the response to MSP2 was poor, with no change observed in the anti-MSP2 antibody titres compared to baseline values. Although no systemic reactions occurred, approximately half the subjects had mild pain at the injection site in the few days following vaccination.

Subsequently, a phase 1-2b double-blind randomised placebo-controlled trial was carried out in 120 5-9 year-old children living in the Wosera (25). The subjects receiving the vaccine (n=60) were injected intramuscularly with 15 g of each antigen on two occasions four weeks apart. The same number of children received the placebo, physiological saline emulsified with Montanide ® ISA720. The vaccine induced significant antibody responses to all three antigens; no severe or serious adverse events occurred in children who received vaccine or placebo (26). In this trial there was a 62% reduction in parasite density among children who were not pretreated with sulfadoxine-pyrimethamine. The vaccinated children had a lower prevalence of parasites carrying the 3D7 MSP2 allelic form (corresponding to that in the vaccine) and a higher incidence of symptomatic malaria associated with parasites of the FC27 MSP2 allelic form. This result is the primary rationale for proceeding with the development of the MSP2-C1 vaccine to be tested in the current study.

### 2.3.3 Clinical Experience with Montanide® ISA720

In addition to the Combination B trials discussed above Montanide® ISA720 formulations of five other experimental malaria vaccines (27-32) and one experimental HIV vaccine (33) have been tested in humans. The antigens in these vaccines have been either recombinant proteins or long synthetic peptides. Including the Combination B trials discussed above, Montanide® ISA720, with or without antigens has been given to more than 450 subjects, 120 of whom were children aged 5-9 in the Combination B Phase 1-2b trial in Papua New Guinea. In these trials more than 200 volunteers have received Montanide® ISA720 without any antigen, the largest volume being 1.8 ml. The adjuvant alone was well tolerated with no SAEs reported. Antigens formulated in Montanide® ISA720 were also mostly well tolerated and no SAEs were reported. Systemic reactions such as fatigue, myalgia and headache occurred in a minority of volunteers and were not more common than for some commonly used vaccines.

The most common adverse event observed in trials using Montanide ISA720 is local reactogenicity (34). The acute reactions are characterized by of pain, swelling, induration, sterile abscess, and granuloma formation. These have been generally mild to moderate in 33 to 91% of volunteers. In the single Phase 2 trial in children in an endemic area the rate was 12% (26). The overall rate for mild and moderate acute local reactions is similar to that observed with licensed pediatric vaccines such as DT (standard pediatric dose) (55% mild/moderate local reactions) or dT (low dose vaccine) (52% mild/moderate reactions) in 6-year-old children. Severe local reactions occurred only with 5 vaccinees who received the vaccine via the intramuscular route for a cumulative rate of 1%. This proportion is not greater than that observed for some licensed vaccines (17% severe local reactions with DT and 11% severe local reactions with dT) (35). Severe local reactions were seen much more commonly in trials administering the vaccine subcutaneously. In these 2 trials (30) up to 44% of recipients of higher doses were not revaccinated due to local reactions. Acute local reactions were seen frequently with pain, swelling and/or induration most common. In the HIV vaccine study (33) sterile abscess and granuloma formation was seen in some volunteers, particularly those receiving the high antigen dose (2 mg), which was far in excess of that given in the malaria vaccine studies or that planned in this study. In most studies the vaccine was injected intramuscularly and when this route was used the majority of local reactions were mild to moderate with a cumulative rate of 1% for severe reactions. In contrast, severe local reactions were seen more commonly in the two studies in which the vaccine was administered subcutaneously (31, 32).

Delayed local reactions as seen in the Combination B studies (see Section 2.3.2) occurred in some volunteers in the majority of other trials with antigens formulated in Montanide® ISA720. Over all of the studies approximately 11% of volunteers developed these reactions, which were characterized by pain and swelling at the injection site occurring 10-28 days after vaccination. They resolved without sequelae usually in a few days but in some cases several weeks. There was a trend indicating that the rate and severity of these delayed reactions was increased with higher antigen doses and multiple injections.

One trial which assessed the safety and immunogenicity of AMA1 formulated in Montanide ISA720 was carried out at the Royal Brisbane Hospital (28). In this dose-escalating study three groups of volunteers were vaccinated intramuscularly with 5 g (n=10), 20 g (n=10) or 80 g (n=9) of AMA1, respectively, in 0.5 ml of formulated vaccine at 0, 3 and 6 months. No vaccine-related adverse SAEs were recorded but most subjects had a mild to moderate, transient local reaction after the first vaccination. One subject with a severe local reaction after the first vaccination (5 g) lasting five days was treated with acetylsalicylic acid and given no further doses of vaccine. Another subject developed a delayed local reaction 12 days after the third dose (80 g) of vaccine. Discomfort persisted for two weeks, whereas swelling took more than 1 month to resolve.

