### 7.2.2 Determination of Severity

Severity of AEs will be assessed by the investigator as described in **Appendices 2, 3, and 4**. AEs not included in **Appendices 3 and 4** will be graded for severity using the following definitions:

Grade 0 (None):

Grade 1 (Mild): No effect on activities of daily living.

Grade 2 (Moderate): Partial limitation in activities of daily living (can complete  50% of baseline), or treatment given.

Grade 3 (Severe): Activities of daily living limited to < 50% of baseline, or medical evaluation required.

Grade 4 (Life- Extreme limitation in activity, significant assistance required;

threatening): immediate medical intervention or therapy required to prevent death.

Grade 5: Death.

Intensity of solicited AEs will be assessed by the investigator as described in **Appendix 2.** All laboratory AEs will be graded in severity following the toxicity table in **Appendix 3**. Unexpected adverse events not described in the protocol will be graded according to the common toxicity table in **Appendix 4**.

The maximum observed intensity reported for any AE is recorded for the entire duration of the AE.

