### 7.5.1 Criteria for Stopping an Individual Volunteer’s Further Vaccination

A. *Local Reactions*: Investigator discretion

B. *Systemic AEs*: Individual participants will be withdrawn from further immunisation if they develop a Grade 3 AE beginning within two days after immunisation and persisting at Grade 3 48 hours if the AE is malaise, myalgia, fatigue, fever, headache, or joint pain, or if the subject has any other Grade 3 AE considered to be associated with vaccination, or if they have any vaccine-related SAE.

C. *Laboratory AEs*: Individual participants will be withdrawn from further immunisation for any Grade 2 laboratory AE that lasts for ≥48 hours or any Grade 3 laboratory AE considered possibly, probably or definitely associated with immunisation.

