### 10.3.2 Immunisation

Possible local vaccine reactions include pain, swelling, erythema, induration, nodule formation, limitation of limb movement for several days, lymphadenopathy, or pruritis at the injection site. Delayed type local injection site reactions may be seen with the Montanide® ISA720 adjuvant. Systemic reactions such as fever, chills, headache, fatigue, malaise, myalgia and joint pain may also possibly occur. Immediate hypersensitivity reactions including urticaria, anaphylaxis or other IgE mediated responses are possible as with any vaccine. As with any investigational vaccine, there is a theoretical possibility of risks about which we have no present knowledge. Volunteers will be informed of any such risks should further data become available.

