Appendix 2 - Assessment of Adverse Event Severity

| **Adverse Event** | **Grade** | **Intensity** |
| --- | --- | --- |
| Pain at injection site | 0 | Absent |
|  | 1 | Pain that is easily tolerated |
|  | 2 | Pain that interferes with daily activity |
|  | 3 | Pain that prevents daily activity |
| Erythema at injection site | 0 | 0 mm |
|  | 1 | >0 - <20 mm |
|  | 2 | >20 - <50 mm |
|  | 3 | >50 mm |
| Swelling at injection site | 0 | 0 mm |
|  | 1 | >0 - <20 mm |
|  | 2 | >20 - <50 mm |
|  | 3 | >50 mm |
| Induration at injection site | 0 | 0 mm |
|  | 1 | >0 - <20 mm |
|  | 2 | >20 - <50 mm |
|  | 3 | >50 mm |
| Fever (oral) | 0 | <37.5°C |
|  | 1 | 37.6°C - 38.0°C |
|  | 2 | >38.0°C – 39.0°C |
|  | 3 | >39.0°C |
| Headache | 0 | None |
|  | 1 | Headache that is easily tolerated |
|  | 2 | Headache that interferes with daily activity |
|  | 3 | Headache that prevents daily activity |
| Nausea | 0 | None |
|  | 1 | Nausea that is easily tolerated |
|  | 2 | Nausea that interferes with daily activity |
|  | 3 | Nausea that prevents daily activity |
| Malaise | 0 | None |
|  | 1 | Malaise that is easily tolerated |
|  | 2 | Malaise that interferes with daily activity |
|  | 3 | Malaise that prevents daily activity |
| Myalgia | 0 | None |
|  | 1 | Myalgia that is easily tolerated |
|  | 2 | Myalgia that interferes with daily activity |
|  | 3 | Myalgia that prevents daily activity |
| Arthralgia | 0 | None |
|  | 1 | Joint pain that is easily tolerated |
|  | 2 | Joint pain that interferes with daily activity |
|  | 3 | Joint pain that prevents daily activity |
| Urticaria | 0 | None |
|  | 1 | Requiring no medications |
|  | 2 | Requiring PO or topical treatment or IV medication or steroids for <24 hours |
|  | 3 | Requiring IV medication or steroids for >24 hours |

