Appendix 4– Tables for Grading Adverse Events

These tables are to be used to grade unexpected adverse events not described in Appendices 2 and 3.

| **Vital Signs*** | **Grade 1**  **(Mild)** | **Grade 2**  **(Moderate)** | **Grade 3 (Severe)** | **Grade 4**  **(Life threatening)** |
| --- | --- | --- | --- | --- |
| Tachycardia –  beats per minute | 110-120 | 121-140 | >140 | >160 with symptoms** |
| Bradycardia –  beats per minute | 50-54 | 45-49 | <45 | <35 with loss of consciousness |
| Hypertension (systolic) – mm Hg (with repeat testing at same visit) | 141-150 | 151-170 | >170 | >200 with symptoms** |
| Hypertension (diastolic) –  mm Hg (with repeat testing at same visit) | 91-100 | 101-110 | >110 | >120 with symptoms** |
| Hypotension (systolic) –  mm Hg (with repeat testing at same visit) | 85-89 (and symptomatic) | 80-84 (and symptomatic) | <80 | < 70 with loss of consciousness |
| * Participant should be at rest for measurement of vital signs  ** Severe headache, chest pain, altered consciousness, or other signs of acute organ damage | | | | |

| **Systemic** | **Grade 1 (Mild)** | **Grade 2  (Moderate)** | **Grade 3 (Severe)** | **Grade 4  (Life threatening)** |
| --- | --- | --- | --- | --- |
| Anorexia | Loss of appetite without decreased oral intake lasting greater than 48 hours | Loss of appetite associated with decreased oral intake without significant weight loss | Loss of appetite associated with significant weight loss | NA |
| Vomiting | 1-2 episodes/24 hours | > 2 episodes/24 hours | Prevents daily activity, requires outpatient IV hydration | Requires hospitalization |
| Diarrhea | 2-3 loose stools/24 hours | 4-5 loose stools/24 hours | >6 loose stools or requires outpatient IV hydration | Requires hospitalization |
| Constipation | NA | Persistent constipation requiring regular use of dietary modifications, laxatives, or enemas | Obstipation with manual evacuation indicated | NA |
| Fatigue | No interference w/activity | Some interference w/activity | Significant, prevents daily activity | NA |
| Arthritis | Mild pain with inflammation, erythema or joint swelling – but not interfering with function | Moderate pain with inflammation, erythema or joint swelling – interfering with function, but not with activities of daily living | Severe pain with inflammation, erythema or joint swelling –and interfering with activities of daily living | NA |

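### Fatigue is an expected reaction named in a stopping rule, yet it is missing from the solicited-event table and graded only among unexpected events

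*Protocol*

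**What the plan says.** Three places in the protocol treat fatigue as an anticipated event.

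- Section 2.3.3, on earlier ISA720 trials: "Systemic reactions such as fatigue, myalgia and headache occurred in a minority of volunteers".
- Section 10.3.2, on risks in this trial: "Systemic reactions such as fever, chills, headache, fatigue, malaise, myalgia and joint pain may also possibly occur".
- Section 7.5.1B, the individual rule for a persisting Grade 3 systemic event, applies "if the AE is malaise, myalgia, fatigue, fever, headache, or joint pain".

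Three places govern how such an event is graded.

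- Section 7.2.2: "Intensity of solicited AEs will be assessed by the investigator as described in" Appendix 2. That table covers four injection-site items plus fever, headache, nausea, malaise, myalgia, arthralgia and urticaria. It has no fatigue row.
- Section 7.2.2 again: "Unexpected adverse events not described in the protocol will be graded according to the common toxicity table in" Appendix 4.
- Appendix 4, which does have a fatigue row, opens with: "These tables are to be used to grade unexpected adverse events not described in Appendices 2 and 3".

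**The concern.** Safety and tolerability are the primary objective. Section 9.1.1 gives the purpose as estimating event rates and patterns of adverse events, and Section 9.1.2 tabulates and tests them by Preferred Term. For that to work, reactions expected from this type of vaccine should be elicited in the same way, so that their rates can be read against each other.

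The split between Appendix 2 and Appendix 4 is the protocol's only indication of which systemic symptoms are solicited. If the diary cards and case report forms are built from Appendix 2, malaise, myalgia and headache get a prompt and fatigue does not. A reaction that the protocol itself expects, and acts on in Section 7.5.1B, could then depend on whether the volunteer mentions it.

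**Working it through.** The protocol states no figure on this point, so the check sets the passages side by side.

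**Step 1. Where each of the six symptoms in Section 7.5.1B appears.**

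| Symptom | Named in 2.3.3 | Named in 10.3.2 | Row in Appendix 2 | Row in Appendix 4 |
| --- | --- | --- | --- | --- |
| Malaise | no | yes | yes | no |
| Myalgia | yes | yes | yes | no |
| Fatigue | yes | yes | **no** | **yes** |
| Fever | no | yes | yes | no |
| Headache | yes | yes | yes | no |
| Joint pain | no | yes | yes (arthralgia) | no |

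Five of the six are in Appendix 2. Fatigue is the exception, although it is one of only three systemic reactions that Section 2.3.3 names from earlier ISA720 trials.

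**Step 2. Does fatigue meet the conditions for Appendix 4?** Section 7.2.2 sets two: the event is unexpected, and the protocol does not describe it. Fatigue meets neither, because Sections 2.3.3, 7.5.1B and 10.3.2 all name it. The opening line of Appendix 4 also sets two: the event is unexpected, and it is not in Appendices 2 or 3. Fatigue meets the second only because Appendix 2 leaves it out. On either wording, its place in Appendix 4 contradicts the rest of the protocol.

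**Step 3. Does the placement change the severity threshold?** Grade 3 malaise in Appendix 2 is "Malaise that prevents daily activity". Grade 3 fatigue in Appendix 4 is "Significant, prevents daily activity". The lower grades also run in parallel, from no real interference to some interference. The threshold that feeds Section 7.5.1B is therefore the same whichever table is used.

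**Step 4. Does the placement change what is recorded?** Sections 6.5 and 7.2.1 describe the diary. Among systemic items they name only oral temperature; every other systemic complaint falls under an open entry. Staff review the diaries at clinic visits to Day 28 and record adverse events from them (Section 7.2.1). Section 9.1.2 tabulates all adverse events and does not restrict them to solicited ones. On this text fatigue can reach the analysis. Whether it is prompted for in the same way as malaise, myalgia and headache depends on the diary card, which is not in the document.

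**Step 5. Scale.** Section 3.2 gives 12 vaccinees per dose level, so each volunteer whose fatigue is or is not recorded moves the rate for that dose by 1/12 = 8.3 percentage points. How many volunteers might be affected cannot be derived, because the protocol gives neither a fatigue rate nor a capture fraction.

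**The case against.** The strongest reply is that this is a labelling slip without consequence. Appendix 2 is a severity table, and Section 7.2.2 says how the intensity of solicited events is judged, not that the table lists everything volunteers are asked about. The diary text does not name headache, myalgia or malaise either. There are telephone calls on Days 1 and 21 and visits on Days 3, 7, 14 and 28 after each dose, so severe fatigue is unlikely to be missed. Most of this stands, and it rules out five stronger readings that a reader might be tempted to make.

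- *The fatigue rate is biased low.* Not shown. The open diary entry, the staff review and the tabulation of all adverse events are consistent with full capture.
- *The appendix placement splits fatigue from malaise.* It does not. Sections 7.5.1B and 10.3.2 already name them as separate symptoms, and tabulation by Preferred Term follows the reported term whichever table grades it.
- *Fatigue has a stopping rule of its own whose working is distorted.* The rule is shared by six symptoms, and the Grade 3 wording matches.
- *Fatigue would be misreported to the regulator as unexpected.* Section 7.3 does not define that word by Appendix 4, and Section 10.3.2 lists fatigue as a possible reaction.
- *Chills, named in Section 10.3.2 but in no table, cannot be graded.* The general scale in Section 7.2.2 covers them.

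The reply does not remove the contradiction in Step 2. Nor does it explain why five of six symptoms under one rule are tied to solicited events and the sixth is not. The protocol offers no other list of solicited systemic symptoms, so whoever designs the diary card has only Appendix 2 to work from.

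**Conclusion.** The contradiction is established from the text alone. Fatigue is a known and anticipated reaction named in a Grade 3 rule. It is the only one of that rule's six symptoms outside Appendix 2, and it is graded in a table whose stated conditions it does not meet.

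The consequence is a possible difference in how consistently fatigue is elicited compared with malaise, myalgia and headache in the primary safety analysis. That step assumes that the diary prompts follow Appendix 2, which the document neither confirms nor excludes. No numerical effect is claimed. The point deserves action because it touches the primary objective and costs very little to put right.

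**What to change.** Reconcile Sections 7.2.2, 7.5.1B and 10.3.2 with Appendices 2 and 4. Move the existing fatigue row, with its grade wording unchanged, from Appendix 4 to Appendix 2. Make sure that the Day 0-6 and Day 7-13 diary cards prompt for fatigue in the same way as for the other systemic symptoms in Appendix 2. The rule in Section 7.5.1B is not altered. The change is best made before Cohort 1 is vaccinated: the two dose levels are enrolled consecutively, so a change between cohorts would itself make ascertainment differ by dose.

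The cost is a wording change to the protocol, diary card and case report form. Each volunteer gains one line a day on two seven-day cards after each of three doses, which is 2 x 7 x 3 = 42 extra entries. The recorded adverse event rate may rise slightly. No visit, sample or test is added.

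Two additions are optional: a per-volunteer count of fatigue or malaise combined, alongside the separate terms, and a specific grading row for chills.
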